## **5 TRIAL DESIGN**

### **5.1 Design overview**

This is a prospective, multicentre, randomized, stratified, parallel-group, double-blind trial comparing placebo with 45 mg pioglitazone as add-on therapy to 100 mg riluzole in amyotrophic lateral sclerosis (ALS) in 220 enrolled patients. For entry, the El Escorial Criteria for the diagnosis of ALS will be used (<http://www.wfnals.org>). The patients have to be stable on riluzole at least three months prior to randomization. The trial requires an initial screening visit (V0), one baseline visit (V1), 4 subsequent control visits (V2 – V5), and a final visit (V6). The duration of study participation for patients completing the study is 18 months.

After patients are screened for inclusion and exclusion criteria, they are randomly assigned to treatment with either placebo or 45 mg pioglitazone according to their stratum (see section 6.10.1). The dosage will be increased step wise: 15 mg once daily will be applied during the first two weeks, 30 mg once daily during week 3 and 4 and 45 mg once daily from week 5 on up to the end of the study. The study drug will be tablets of 15/30/45 mg base or matching placebo. The drug will be administered orally. In patients with gastrostomy, tablets will be crushed and administered via the feeding tube.

### **5.2 Trial procedures**

On enrolment in the trial, a patient will undergo a physical examination and a detailed medical history will be obtained.

#### **Efficacy Variables**

Efficacy variables will be determined at the study site by using standard methods.

- Survival / Date of death requiring a death certificate
- ALS-FRS-R
- Euroqol EQ-5D
- Tracheotomy or NIV (yes/no, date of event, reason for intervention, duration per day, if applicable)

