### 5.3 Trial visits schedule

For the planned trial visits schedule the inclusion date is considered to be the reference date. The dates of the following visits specified in the protocol are calculated in relation to the date of this visit.

If the time of a visit is modified in relation to the visits schedule, the times of the following visits will always be determined with respect to the inclusion visit. The time window for each planned visit will be

± one week. The investigator must always ensure that the patient receives a sufficient quantity of treatment units to cover the period up to the next visit. The visits schedule is not modified by any unscheduled visits.

In the case of premature interruption of the study treatment, a complete examination identical to visit V6 should be carried out. Premature study discontinuation must be noted as such on the case report form. Patients prematurely leaving the study must not rejoin the trial.

Additionally a study physician will contact the patient by telephone 1, 3, 9, and 15 months after study enrolment.

An overview including the time schedule for all visits is given in table 5.2.

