#### 5.6 *Sequence and duration of trial periods*

The duration of treatment will be 18 months resulting in a duration of the trial of about 24 months; 1 month will be reserved for screening, three for recruitment, 18 months for the treatment period, and two for an observational follow-up period after the interventional period. Then the functional and survival data will be analysed.

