#### 7.1.2 Serious adverse event (SAE)

A serious adverse event is any untoward medical occurrence that at any dose:

- Results in death,
- is life-threatening,
- requires in-patient hospitalisation or prolongation of existing hospitalisation,
- results in persistent or significant disability/incapacity,
- is a congenital anomaly, birth defect, or
- may require intervention, as a medically important event, to prevent one of the above criteria or may expose the patient to danger, even though the event is not immediately life threatening or fatal or does not result in hospitalisation (examples: allergic bronchospasm treated on an outpatient basis, convulsions not requiring hospitalisation or abnormal laboratory parameters compromising patient safety).

The following points should be taken into account when evaluating the seriousness of an adverse event:

- The life-threatening criterion indicates that there was an immediate risk of death at the time of its occurrence. This does not mean that if the adverse event had occurred in a more severe form it would have lead to death.

The following are not considered to be serious adverse events:

- An event causing a brief visit to a hospital consultation, an open-door or day hospital,
- outpatient treatment in the emergency department although the reason for which this treatment was instituted may be serious, or
- admission to hospital (more than one night in a hospital bed) including surgical operations planned before or during the study if the condition was present before the study and provided that it does not worsen during the study.

The following are considered to be serious adverse events even if they do not comply with the definition:

- Adverse events caused by misuse or overdose,
- Any pregnancy discovered during the study.

Note: a state of pregnancy is an exclusion criterion. Hence contraceptive measures are necessary in women with childbearing potential throughout the study. However if pregnancy is discovered during the study the trial treatment must immediately be discontinued and the pregnancy followed to term.

N.B. a non-serious adverse event designates any other event not corresponding to the above-defined criteria.

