## **7.2 Monitoring and recording of adverse events**

At each visit after V0 the investigator must question the patient about the occurrence of any adverse event and note any abnormal laboratory findings. A neutral question such as "since the last visit have you felt any untoward or unusual symptoms other than those related to your illness?" elicits any adverse events experienced by the patient.

Whatever the relation to the study treatment is, any adverse event such as those described in section 7.1 spontaneously reported by the patient or observed by the investigator must be reported on the appropriate page of the case report form. For each adverse event, the following information should be documented:

- Description of the event (diagnosis and symptoms in verbatim terms)
- Outcome
- Seriousness
- Duration (start date and stop date)
- Severity (mild, moderate or severe); see section 7.1.4
- Frequency (permanent, intermittent)
- Causal relationship with the study treatment according to the scale shown in section 7.3
- Corrective actions including measures taken for the study treatment

The study number, patient number and investigator's signature must also be noted.

Any clinically significant event including any abnormal laboratory result or vital sign must be followed-up until it has completely disappeared or the investigator has assessed its sequelae, even after the end of the study.

The results of any complementary tests performed (laboratory tests, ECG, X-rays etc.) must be dated and appended to the CRF. The investigator must evaluate each adverse event and give his/her opinion about the causal relationship with the drug(s) used.

A period of 14 days for follow up of AEs after the patient has routinely or prematurely terminated the study seems sufficient.

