### 8.2.5 Efficacy evaluation

The primary objective of the study is to demonstrate the superiority of the test treatment compared to the standard treatment in terms of survival.

The study will be conducted according to a two-stage group sequential test design with possible sample size adaptation after the planned interim analysis. The overall type-I-error rate is set at  $\alpha = 0.025$  (one-sided).

The following null hypothesis  $H_0$  will be tested against the alternative hypothesis  $H_A$  ( $\alpha = 0.025$ , one-sided):

$$H_0: \lambda_2 / \lambda_1 \geq 1$$

$$H_A: \lambda_2 / \lambda_1 < 1$$

where  $\lambda_2 / \lambda_1$  is the hazard ratio,  $\lambda_1$  denotes the hazard in the standard group and  $\lambda_2$  in the test group. The hazard ratio is assumed to be constant across time.

The null hypothesis will be tested using the log-rank test.

The first interim analysis will be conducted after observation of a total of 31 deaths. The null hypothesis will be rejected at the first interim analysis if the calculated test statistic exceeds the critical value 2.797. In this case, the study may be stopped. If the null hypothesis will not be rejected, the study may be continued until the pre-specified number of 61 deaths (accumulated number of deaths) or a recalculated number of deaths based on the effect size estimation of the first interim analysis were observed.

Data from all subjects will be considered when calculating the second stage log-rank test statistic. At the final (second) analysis, the null hypothesis will be rejected if the calculated inverse normal test statistic exceeds the critical value 1.977.

This procedure preserves the overall (experiment-wise) type I error rate of  $\alpha = 0.025$  in a strong sense.

For estimating the treatment effect, the hazard ratio and the corresponding two-sided 95% repeated confidence interval will be provided.

All other group comparisons are hypothesis generating in nature, i.e., p-values resulting from these statistical tests will be interpreted in the exploratory sense.

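### No vital-status check is scheduled at the 31- and 61-death data cuts or in the 2-month follow-up, although the final analysis needs observation beyond the last scheduled contact at month 18

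*Protocol*

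**What the plan says.** Mortality, defined as death only, is the primary endpoint (section 3). Section 5.2 names the item to be collected as "Survival / Date of death requiring a death certificate".

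On contacts, section 5.3 states "Additionally a study physician will contact the patient by telephone 1, 3, 9, and 15 months after study enrolment". Clinic visits fall at months 2, 6, 12 and 18, with a laboratory check at the general practitioner at month 1. The schedule in section 1 and Table 5.2 both end at V6, and section 5.1 says "The duration of study participation for patients completing the study is 18 months".

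On timing of the analyses, section 8.2.5 says "The first interim analysis will be conducted after observation of a total of 31 deaths", with the final analysis at 61 deaths or a recalculated number. Section 8.1 expects these at 11.1 and 21 months, after 6 months of accrual. Section 5.6 lists, after treatment, "two for an observational follow-up period after the interventional period. Then the functional and survival data will be analysed".

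On reporting, an event that "Results in death" is an SAE (section 7.1.2) and is faxed within one working day of knowledge (section 7.4.2). The reporting duty ends 2 weeks after the end of the study (section 7.4.1). For adverse events, section 7.2 says "A period of 14 days for follow up of AEs after the patient has routinely or prematurely terminated the study seems sufficient".

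**The concern.** A death-triggered cut falls on an arbitrary calendar day. By then most in-study deaths will have been reported, but a living patient is known to be alive only on the date of the last contact, which may be up to three months earlier. A patient past month 18 has no further scheduled contact at all.

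If deaths are counted to the cut and survivors are censored at last contact, the risk sets in that last stretch hold the patients who died but few of those who lived. Deaths there add little to the log-rank statistic, and the Kaplan-Meier curve drops too steeply. If instead all data stop at month 18, some of the 61 deaths are not available. Either way, the planned death counts deliver less information than section 8.1 assumes. A SAP can choose a censoring rule, but it cannot supply survivor status that nobody collected.

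**Working it through.** **Inputs (section 8.1).** 18-month survival of 60% vs 78%; one-sided alpha 0.025; critical values 2.797 and 1.977; 31 and 61 deaths; 198 subjects (99 per arm); accrual 6 months; analyses at 11.1 and 21 months. Contacts (section 5.3 and the schedule tables) are at months 0, 1, 2, 3, 6, 9, 12, 15 and 18.

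**Reproducing the plan.**
- HR = ln 0.78 / ln 0.60 = 0.4864.
- Schoenfeld: 4 × (1.960 + 0.842)² / (ln 0.4864)² = 60.4, so 61 deaths.
- The two-stage O'Brien-Fleming boundaries come out at 2.797 and 1.977, and power with looks at 31 and 61 deaths is 80.1%.
- Monthly hazards: −ln 0.60 / 18 = 0.0284 and −ln 0.78 / 18 = 0.0138. With uniform accrual over 6 months, mean survival at calendar month 21 is 0.6007 and 0.7802. Expected deaths are 99 × 0.3993 + 99 × 0.2198 = 61.3. At 11.1 months the figure is 30.7.

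The plan's figures therefore hold, provided patients are observed up to the calendar cut.

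**How far the schedule falls short at month 21.** Patients enrolled in the first 3 of the 6 accrual months, half the total, are past their own month 18.
- Alive and past the last scheduled contact: 49.5 × 0.5752 + 49.5 × 0.7641 = 66.3 of 198, where 0.5752 and 0.7641 are mean survival over months 18 to 21.
- Deaths after a patient's own month 18: 49.5 × (0.60 − 0.5752) + 49.5 × (0.78 − 0.7641) = 2.0, leaving 59.3 of the 61.3.
- At the final cut, the last contact is on average 1.95 months old and 8.9% of person-time is unobserved. At the interim cut the figures are 1.5 months and 17%.

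**Effect.** 20,000 simulated trials per scenario, each look tested singly against its own critical value:

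| Handling | Final rejection | Interim rejection |
|---|---|---|
| Survivors' status known at the cut | 79.0% | 19.3% |
| Deaths to the cut, survivors censored at last contact | 75.3% | 17.1% |
| All data stop at each patient's month 18 | 76.8% (about 58 deaths) | 19.3% (no one past month 18 yet) |

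The final loss is 79.0 − 75.3 = 3.7 points or 79.0 − 76.8 = 2.2 points. The interim loss under the second handling is 19.3 − 17.1 = 2.2 points.

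Under the second handling, control-arm Kaplan-Meier survival at 18 months reads 0.521 instead of 0.595 at the final analysis. At the interim, 9-month survival reads 0.662 instead of 0.768. The hazard ratio moves from 0.482 to 0.493 (final) and from 0.478 to 0.485 (interim). Null rejection is 2.3% vs 2.3% (final) and 0.22% vs 0.24% (interim).

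Cutting both deaths and survivors at last contact would remove the distortion of the curves, but it discards the deaths in between. In a separate run on the same assumptions it took final rejection from about 78% to about 74%.

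**The case against.** The strongest reply is that the harm depends on a censoring rule the protocol does not state. Data-cut conventions are ordinary SAP content, and section 8.2.7 also promises an interim SAP. That stands as far as the rule goes. It does not answer the missing data: with no check at the cut, each rule available to the SAP loses either deaths or survivor time.

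It is also fair that dated visits and calls already give a date last known alive, that section 5.2 already specifies tracheotomy and NIV with dates, and that patients off study drug are to be followed where possible (section 7.6). Extra form rows at every visit would therefore add nothing. Unscheduled visits and the low expected loss to follow-up (below 1%) would soften the simulated effect.

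Stronger readings are tempting but not supported:
- A reader might infer that deaths in the 2-month follow-up are known while survivors are not. SAE reporting ends 2 weeks after end of study, so after that neither has a described route.
- A reader might infer that nothing at all happens after month 18. The 14-day AE window and 2-week SAE window exist, and section 7.6.1 asks for a visit 2 weeks after premature withdrawal where possible. For completers, the tables list no contact in those windows.
- A reader might count every death expected between months 18 and 20 as affected. That assumes everyone is followed to month 20, whereas the event-driven final analysis on the section 8.1 timetable involves about 2 deaths after a patient's month 18.
- A reader might infer a biased test. The simulation shows no type I error inflation and almost no change in the hazard ratio.

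Finally, the visit text after V2 in section 5.3 is partly illegible in the copy reviewed. A contact described there cannot be excluded, although neither table has a column after V6.

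**Conclusion.** The point holds as a gap in data collection. Nothing scheduled establishes who is alive at the two data cuts or at the end of the 2-month follow-up, while section 8.1 relies on observation past month 18 for about half the patients.

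The size is modest: about 2 to 4 points of power at the final analysis. At the interim the loss is about 2 points, and Kaplan-Meier survival is visibly too low, when deaths run to the cut and survivors are censored at last contact. The validity of the test is not in question.

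This rests on exponential survival, uniform 6-month accrual as in section 8.1 (section 5.6 reserves three months for recruitment), no drop-out, every scheduled contact kept, the same ascertainment in both arms, and no evidence of life other than scheduled contacts.

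**What to change.** In section 5.3 and both schedule tables, add one vital-status telephone check of every randomised patient not known dead, including those off study drug, at three points: the interim data cut, the final data cut, and the end of the 2-month follow-up. Record the date of death or the date last known alive, and censor survivors at the common cut-off date.

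The cost is a few short calls per surviving patient, by staff who already make T1 to T4, and a delay of perhaps a week or two at each data cut. If the illegible part of section 5.3 already describes such a contact, it only needs to be carried into the tables and tied to the data cuts.

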#### **Safety Variables**

- Blood cell count (RBC, WBC, Hb, Hct, MCV, MCH, MCHC)
- ASAT
- ALAT
- CK

- Creatinine
- Fasting blood glucose
- Beta-HCG

Table 5.1: Blood Samples and Volumes

| SAFETY                         | Sample Volume (ml)   | V0        | V1    | V2 (GP) | V3      | V4      | V5       | V6       |
|--------------------------------|----------------------|-----------|-------|---------|---------|---------|----------|----------|
|                                |                      | Screening | Day 1 | Month 1 | Month 2 | Month 6 | Month 12 | Month 18 |
| blood cell count               | EDTA (2.7)           | X         | X     |         | X       | X       | X        | X        |
| ALAT                           | Serum (4.9)          | X         | X     | X       | X       | X       | X        | X        |
| ASAT                           |                      | X         | X     | X       | X       | X       | X        | X        |
| CK                             |                      | X         | X     | X       | X       | X       | X        | X        |
| Creatinine                     |                      | X         | X     | X       | X       | X       | X        | X        |
| Fasting blood glucose          | NAF (1.2)            | X         | X     | X       | X       | X       | X        | X        |
| beta-HCG                       | Serum (1.1) or urine | X         |       |         |         |         |          |          |
| Pioglitazone-level             | Serum (9.0)          |           | X     |         | X       | X       | X        | X        |
| Total Blood Volume (ml) |                      | 9.9       | 17.8  | 4.9     | 17.8    | 17.8    | 17.8     | 17.8     |

The calculated volume of blood needed for the different laboratory determinations at the different visits is given in table 5.1. The maximal calculated volume of blood taken of patients who have completed the whole study is approximately 105 ml within 18 months.

Any deviation of laboratory parameters from normal ranges will be documented and followed up as appropriate. Clinically significant deviations observed in the screening visit and during the study will be documented in the Case Report Form.

## Adverse Events

Adverse events observed by the investigators or reported by the patients will be documented as described in chapter 7.

## Demographic Data

- Date of Birth
- Sex
- Origin
- Familial status

## Medical History

Clinically significant conditions that stopped within the last 5 years and concomitant diseases will be documented. In addition, following items have to be addressed specifically:

- Smoking habits within the last 12 months
- Alcohol consumption

## Physical Examination

- Height
- Weight
- Radial pulse (with the patient in sitting position for at least 5 minutes)
- Blood pressure (according to Riva Rocci using calibrated sphygmomanometers, the patient has to be in a sitting position for at least 5 minutes, blood pressure will be measured twice within 5 minutes, the mean of both measurements will be calculated)
- Any abnormalities detected in:
  - Head and neck
  - Ear, nose, throat
  - Eyes
  - Cardiovascular system
  - Respiratory system
  - Abdomen
  - Extremities and back
  - Lymph nodes
  - Skin
  - Neurological
  - other relevant abnormalities

### 5.3 Trial visits schedule

For the planned trial visits schedule the inclusion date is considered to be the reference date. The dates of the following visits specified in the protocol are calculated in relation to the date of this visit.

If the time of a visit is modified in relation to the visits schedule, the times of the following visits will always be determined with respect to the inclusion visit. The time window for each planned visit will be

± one week. The investigator must always ensure that the patient receives a sufficient quantity of treatment units to cover the period up to the next visit. The visits schedule is not modified by any unscheduled visits.

In the case of premature interruption of the study treatment, a complete examination identical to visit V6 should be carried out. Premature study discontinuation must be noted as such on the case report form. Patients prematurely leaving the study must not rejoin the trial.

Additionally a study physician will contact the patient by telephone 1, 3, 9, and 15 months after study enrolment.

An overview including the time schedule for all visits is given in table 5.2.

### **Screening Visit (V0)**

A signed "Informed Consent" will be obtained from each patient prior to initiating any trial procedure. Presence of ALS diagnostic criteria will be documented as well as site of onset and ALS status at entry according to El Escorial criteria, and modified by the Airlie House criteria (<http://www.wfnals.org>). Venous blood will be taken for the determination of blood cell count, creatinine, CK, ASAT, ALAT, fasting blood glucose, and HCG or urine pregnancy test (only in women with child bearing potential). The patients' eligibility will be determined in accordance with the inclusion/exclusion criteria. A detailed medical history will be taken, and concomitant medication will be recorded. A physical examination, including body weight, height, blood pressure, and radial pulse will be performed. Additionally lung function will be assessed by measuring the patient's vital capacity.

### **Visit 1 – Baseline visit (V1)**

Patients eligible for study participation will enter the study site within 4 weeks after the screening visit and will be randomised to one of the treatment arms.

Blood samples for the determination of blood cell count, creatinine, CK, ASAT, ALAT, fasting blood glucose, and pioglitazone baseline level will be obtained. A physical examination, ALS FRS-R, and EuroQol EQ-5D will be performed. The patient will receive study medication according to the randomization list and a study participant card (see appendix IX).

Any changes in the concomitant medication and adverse events before and during visit 1 will be documented.

